### Outcome measures

#### Routine data

Data reported routinely to the Victorian government is entered at the time of consultation by the MCH nurse. In relation to IPV screening, these data include:

• Whether the nurse reports asking about any of three family violence questions to which the answer is yes/no and at what time point: home visit; four weeks, eight weeks, four, eight, twelve or eighteen months.

• Whether the nurse reports making a safety plan

• Whether the nurse reports making a referral

We will compare rates of inquiry, safety plans and referrals between intervention and comparison arms at four weeks, four months and twelve months.

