#### Checklists

These data will only be available in the intervention arm, as they are a screening intervention tool (see below). Nurses use these screening self-completion forms with women and retain these for collection by MOVE research staff. They also record the screening consultation time (three or four months or later) and these will be analysed especially for the three month screening point, when routine data are not recorded.

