#### Intervention development phase – toward a model of sustainable good practice

This phase involved three strategies:

1.We conducted Participatory Action Research (PAR) with four volunteer MCHN consultants (one from each of four intervention MCHN teams) who explored the barriers and sought answers to these problems within their teams. PAR has been defined as ‘collective, self reflective inquiry that researchers and participants undertake, so they can understand and improve upon the practices in which they participate and the situations in which they find themselves’ [38]. Over a six-month period, at regular monthly meetings with MOVE staff, questions derived from earlier feedback in MOSAIC [26], discussion about barriers and enablers of IPV screening practices, and informed by the NPT framework [36] were agreed and nurse consultants took them away to their teams for discussion and feedback. The two groups (nurse consultants and MOVE staff) met over a six month period to discuss team feedback and reach agreement on the major aspects of a good practice model to be outlined in clinical pathways and guidelines. All meetings were recorded on tape and notes derived from them informed further discussion. We also drew on a GP systems intervention then being piloted in the UK (IRIS [23]) for strategies to strengthen links between clinicians and family violence services.

2. A systematic review of interventions (with controlled or comparison designs), guidelines or protocols targeted at improving the response of health care practitioners (HCPs) working with women experiencing IPV, their children and partners using abusive behaviors was conducted using Medline, Cochrane and Campbell Collaboration databases and CINAHL. Further details of the search terms and inclusion/exclusion criteria are available from the authors. Results were synthesized and presented to the nurse consultant and research group and the advisory group of key stakeholders.

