### Screening time

#### The move intervention model

MCH nurses expressed concern about an early screening time (e.g. home visit or four weeks) for the following reasons: (a) women were still recovering from the birth and focused their attention on the baby’s not their own needs; (b) nurses had had insufficient time to establish a trusting relationship with the woman which would make it easier to ask a sensitive question and enable disclosure (c) >30% of Victorian women have had Caesarean section and advised not to drive for six weeks, so are frequently accompanied by someone, making it sometimes challenging to ensure screening safely. Nurses therefore suggested that the optimum screening time would be at a three or four month visit when women could be advised ahead of time that the visit would be focused on their needs and that they would be completing a women’s health checklist. They also suggested that they could ask women not to bring other children if possible; and told accompanying partners that the questions would include discussion of menstruation and breast problems, and that partners may not want to be present. Two teams created an additional woman-focused three month visit, and the other two teams added fifteen minutes to the four month KAS-funded visit to be focused on maternal needs.

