#### Outcome evaluation - primary and secondary outcomes

##### Routine data

With local government permission, we will retrieve routine data about family violence described above for the intervention period for all nurses in both arms of the study. We will seek to retrieve it again in 2013, two years post intervention.

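### The four-month routine-data comparison of inquiry omits the added three-month visit at which two of the four intervention teams screen, so it under-counts the intervention arm

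*Protocol article*

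**What the plan says.** All references are to the protocol article.

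- **Outcome measures, Routine data.** Nurses record whether they asked, and the time points offered are "home visit; four weeks, eight weeks, four, eight, twelve or eighteen months". There is no three-month item. The planned analysis is: "We will compare rates of inquiry, safety plans and referrals between intervention and comparison arms at four weeks, four months and twelve months". Safety plans and referrals are listed as separate items, with no time point attached.
- **The move intervention model.** Nurses preferred to screen at three or four months, and the teams split: "Two teams created an additional woman-focused three month visit, and the other two teams added fifteen minutes to the four month KAS-funded visit". The section Intervention development phase confirms that the arm has four teams ("one from each of four intervention MCHN teams"), so the three-month teams are half of it.
- **Checklists.** The completed forms are available only in the intervention arm, and "these will be analysed especially for the three month screening point, when routine data are not recorded".
- **Outcome evaluation, Routine data.** The source covers both arms: "we will retrieve routine data about family violence described above for the intervention period for all nurses in both arms of the study".
- **Primary outcomes and their reporting.** Outcome 1 can be met by women's report or by nurses' report of screening, and the reporting list takes screening proportions by arm from both the survey and the routine data.

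**The concern.** The visit that the routine system cannot record was created by intervention teams as part of the MOVE model; the article describes no such visit in the comparison arm. Inquiry made there is lost from one arm only. This is differential ascertainment in a source named for a primary outcome, and it works against the intervention.

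The article sees the gap and turns to the checklists. These can describe uptake in the intervention arm, but there is nothing in the comparison arm to set against them. Adding them to the intervention count alone would bias the contrast the other way.

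At stake is the reading of the four-month routine result. A real gain in inquiry could appear much smaller than it is, absent or, in less favourable circumstances, reversed. A later analysis plan cannot recover inquiries that were never entered.

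**Working it through.** **What can be reproduced.** The article gives no expected rate, sample size or power for the routine-data comparison; its sample-size section concerns the mailed survey. There is no stated figure to check, so the following is an illustration of size.

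**Inputs**

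- True gain in inquiry at the MOVE visit: 15 percentage points. This reads the 15% in primary outcome 1 as an absolute difference, which is an assumption.
- s, the share of intervention-arm women in the two three-month teams: assumed 0.5, range 0.3 to 0.7.
- pC, the comparison-arm inquiry rate at four months: not given; 5% to 50% shown.
- pI = pC + 0.15, the true intervention rate at the three- or four-month screen.
- r, the rate at which the three-month teams record a further inquiry at four months: not given; 0 to pC shown.

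**Formula.** The recorded intervention rate at four months is (1 − s)·pI + s·r. Subtracting pC gives

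recorded difference = (1 − s)·0.15 − s·(pC − r).

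**Results for s = 0.5** (percentage points; the true difference is +15)

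| pC | r = 0 | r = pC/2 | r = pC |
|---|---|---|---|
| 5% | +5.0 | +6.25 | +7.5 |
| 10% | +2.5 | +5.0 | +7.5 |
| 15% | 0.0 | +3.75 | +7.5 |
| 20% | −2.5 | +2.5 | +7.5 |
| 30% | −7.5 | 0.0 | +7.5 |
| 40% | −12.5 | −2.5 | +7.5 |
| 50% | −17.5 | −5.0 | +7.5 |

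**Condition for reversal.** The sign changes when pC − r > (1 − s)·0.15/s. For s = 0.5 this is pC − r > 0.15, so the three-month teams must re-ask at a rate more than 15 points below the comparison rate. With no re-asking, the comparison rate must exceed 15%; with re-asking at half the comparison rate, it must exceed 30%.

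**Sensitivity to team size**

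- If r = pC, the recorded difference is (1 − s) × 15: +10.5 for s = 0.3 and +4.5 for s = 0.7.
- If r = 0, reversal needs pC above 0.7 × 0.15/0.3 = 35% for s = 0.3, or above 0.3 × 0.15/0.7 = 6.4% for s = 0.7.

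**Condition for no loss.** The full 15 points appear only if r = pI, that is, if the three-month teams ask again at four months as often as they would have asked at their own MOVE visit.

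**The case against.** **The trial does not rest on routine data alone.** This stands. The women's survey goes to both arms, asks about being asked, disclosure and referral, and is not tied to the routine time points. The sample-size and power statements concern the survey. A reader might infer that the trial's overall result could be reversed; the documents do not support that.

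**The article discloses the gap and nowhere plans to add checklists to the arm comparison.** Both statements are true. Disclosure does not change the comparison that the Routine data section fixes.

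**Reversal rests on assumed inputs.** This stands. The mandate to ask applies at four weeks; nothing in the article shows how often comparison nurses ask at four months. Reversal is possible but should not be predicted.

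**Stronger readings that the text does not carry**

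- *Bias at four weeks.* A reader might infer it from the nurses' preference for later screening. The four-week screen is mandatory for all nurses and the article does not say that intervention teams stop it. If their four-week rate did fall, that would be a real result at that visit and not a recording error.
- *An uninformative twelve-month comparison.* Many mothers seen at twelve months during the implementation year passed the MOVE visit age before it began. But Aim 1 concerns how often nurses ask and refer, and a twelve-month visit in that year is conducted by nurses working with the guidelines, mentors and liaison workers.
- *Certain loss of three-month safety plans and referrals.* Those items carry no time point in the Routine data list. They may be affected, through the general wording in Checklists, but this is not established.

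**Conclusion.** The point holds for the four-month routine-data comparison of inquiry. That comparison, the absence of three-month routine recording, and the use of that visit by two of four intervention teams are all stated in the article. The direction is clear: inquiries are omitted from the intervention arm only.

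The size is not known. With equal team sizes and a true gain of 15 points, half the effect (+7.5) is recorded if re-asking at four months matches the comparison rate. Less re-asking costs more, and reversal needs the conditions shown above. Only re-asking at the full MOVE rate would remove the loss. Team shares, re-asking and comparison rates are assumptions throughout.

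The defect lies in one named source for primary outcome 1, with a possible but unproven extension to safety plans and referrals. It does not touch the survey.

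**What to change.** **Preferred change.** Replace the four-month routine comparison with a three-to-four-month window, defined identically and with the same denominator in both arms. Ask the two three-month teams to log that visit's inquiry, and any safety plan or referral made there, under the four-month routine item.

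**If the routine system does not allow this, or the entries have already been made.** Name the women's survey as the source for the arm contrast in inquiry. Report the four-month routine rate as a likely underestimate, shown separately for the three-month and four-month teams. That split is descriptive, because visit timing was settled by team and not by randomisation.

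**In either case,** keep the checklists descriptive.

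**Cost.** The preferred change needs a data-entry instruction to two teams and a redefined outcome. Three- and four-month screens can then no longer be told apart in the routine file, although the checklists still separate them. Recording practice changes in two intervention teams only, which must be disclosed, as must the fact that the four-month item then includes three-month visits. The fallback needs no change in recording but leans on a survey with an expected response of 55–65%.

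An outcome counted cumulatively per mother would be cleaner, but routine data are described under Blinding (outcome assessment) as anonymised and summarised annually. It is an option only if record-level data can be obtained.

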#### Survey measures

The survey booklet ‘Women’s Experiences of Health Care and Support with a New Baby’ has seven sections: (A) About your baby; (B) About your own health following your baby; (C) Your health care support; (D) Other care and support you receive; (E) Relationships and family; (F) You and your partner; (G) About you. It is designed to maximize women’s safety as it is mailed to her home. Section F includes questions about intimate partner violence measured using Hegarty’s Composite Abuse Scale [29], together with questions about being asked, disclosure (and comfort to disclose), rates of referral and satisfaction measures for herself, her children and in relation to strategies for her partner.

The questionnaire also includes depression and anxiety measures using the DASS-21 [30,31]; women’s experiences of motherhood measured with the Experience of Motherhood Scale [32] and a range of other assessments of women’s experiences.

#### Checklists

These data will only be available in the intervention arm, as they are a screening intervention tool (see below). Nurses use these screening self-completion forms with women and retain these for collection by MOVE research staff. They also record the screening consultation time (three or four months or later) and these will be analysed especially for the three month screening point, when routine data are not recorded.

## Methods

### Theoretical framework

An overarching goal of this study is the development of a sustainable model of MCHN good practice in identification, support and referral of women experiencing IPV. There has been considerable debate about the limitations of programs aimed at enhancing health care professional behavior change [33]. Further, it is now recognized that when interventions themselves are complex (such as the introduction of primary care nurse IPV screening) and operate in a complex environment (such as both state and local government arenas) that attention to theory, process and in particular, context are required if they are to be successfully integrated into routine practice [34]. This requires greater attention to the development, testing and refinement of an intervention before effectiveness testing.

May et al’s Normalization Process Theory [35-37] proposes four domains of work which require particular attention in the design, development, implementation and evaluation cycle of health system and health professional behavior change. We outline in brief how, in relation to the work of MCHN, we interpreted the core NPT concepts in relation to MCH nurse work and incorporated this into all aspects of the design, development, implementation, and process and impact evaluation of this trial. In terms of the core concepts, we interpreted them as related to MCH nursing work as follows:

• Coherence (how MCH nurses interpret, accept and value their role in, and the concept of IPV screening)

• Cognitive participation (how MCH nurses engage with the work: who introduces, leads, maintains and participates in IPV screening)

• Collective Action – involves four components:

∘ Interactional workability – how and when IPV screening is conducted, how screening roles are organized within teams, resources improving nurse/client screening interaction, who is allocated to the work

∘ Relational integration (accountability, knowledge and trust in IPV screening working relationships including team functioning and including nurse safety)

∘ Skill set workability (do MCH nurses think they have the required skills, resources and rewards to conduct IPV screening effectively)

∘ Contextual integration (how well is screening organized, funded and supported in their working context of local and state government)

• Reflexive monitoring ( how do MCH nurses and teams know how effective or well their IPV screening is going)

#### Intervention development phase – toward a model of sustainable good practice

This phase involved three strategies:

1.We conducted Participatory Action Research (PAR) with four volunteer MCHN consultants (one from each of four intervention MCHN teams) who explored the barriers and sought answers to these problems within their teams. PAR has been defined as ‘collective, self reflective inquiry that researchers and participants undertake, so they can understand and improve upon the practices in which they participate and the situations in which they find themselves’ [38]. Over a six-month period, at regular monthly meetings with MOVE staff, questions derived from earlier feedback in MOSAIC [26], discussion about barriers and enablers of IPV screening practices, and informed by the NPT framework [36] were agreed and nurse consultants took them away to their teams for discussion and feedback. The two groups (nurse consultants and MOVE staff) met over a six month period to discuss team feedback and reach agreement on the major aspects of a good practice model to be outlined in clinical pathways and guidelines. All meetings were recorded on tape and notes derived from them informed further discussion. We also drew on a GP systems intervention then being piloted in the UK (IRIS [23]) for strategies to strengthen links between clinicians and family violence services.

2. A systematic review of interventions (with controlled or comparison designs), guidelines or protocols targeted at improving the response of health care practitioners (HCPs) working with women experiencing IPV, their children and partners using abusive behaviors was conducted using Medline, Cochrane and Campbell Collaboration databases and CINAHL. Further details of the search terms and inclusion/exclusion criteria are available from the authors. Results were synthesized and presented to the nurse consultant and research group and the advisory group of key stakeholders.

3. Using a method we have previously used in an international collaboration to develop GP guidelines [39], we facilitated multidisciplinary group discussions between the nurse consultants and study reference group to independently score and then reach agreement about the content and format of the guidelines, clinical pathway and maternal health checklist – a woman’s self-completion screening tool (all available at http://www.latrobe.edu.au/mchr/html/move.html ). A penultimate draft of these materials was presented and finalized at a reference group meeting and further detail of the model’s key elements are presented below.

### Screening time

#### The move intervention model

MCH nurses expressed concern about an early screening time (e.g. home visit or four weeks) for the following reasons: (a) women were still recovering from the birth and focused their attention on the baby’s not their own needs; (b) nurses had had insufficient time to establish a trusting relationship with the woman which would make it easier to ask a sensitive question and enable disclosure (c) >30% of Victorian women have had Caesarean section and advised not to drive for six weeks, so are frequently accompanied by someone, making it sometimes challenging to ensure screening safely. Nurses therefore suggested that the optimum screening time would be at a three or four month visit when women could be advised ahead of time that the visit would be focused on their needs and that they would be completing a women’s health checklist. They also suggested that they could ask women not to bring other children if possible; and told accompanying partners that the questions would include discussion of menstruation and breast problems, and that partners may not want to be present. Two teams created an additional woman-focused three month visit, and the other two teams added fifteen minutes to the four month KAS-funded visit to be focused on maternal needs.

### Maternal health checklist

Evidence from the systematic review suggested that women preferred self-completion screening methods (e.g. paper or computer based) rather than face-to-face screening inquiry (ref). The maternal health checklist was developed as a tear-off pad consisting of an A-5 set of questions for women to self-complete at the agreed consultation which focused on maternal health, rather than the development of the baby, who is the MCH nurses’ primary client. When women arrived at this visit, they were given the checklist and asked to complete it in a quiet corner and let the nurse know when finished. The checklist consists of a set of questions about maternal health, beginning with questions about physical health, such as headache, nipple or bowel problems then moving to those about depression, contraception or drug misuse to the same family violence questions being asked as part of the Key Ages and Stages (KAS) mandatory screening at four weeks. After discussion, MOVE added two further questions to this list. Just before the KAS questions, we added:

*Do you have any problems in your relationships or intimacy with your partner?* and *Has anyone in your household ever humiliated you or tried to control what you can or cannot do?* The first question was seen as useful for women who may want to discuss non-specific problems in the relationship prior to disclosure and the latter because it is central to intimate partner abusive behavior. If a woman ticked any of the relationship or any family violence questions, nurses were asked to initiate a discussion about these in ways that felt appropriate and comfortable. The completed checklist form is retained as part of the study data collection.

### Clinical guidelines and pathway

The eight-page guidelines were designed so that the clinical pathway was on the front page and summarized recommended actions and also feature principles of good practice along the bottom.

These principles are:

• SEEK SUPPORT Consult your team leader, nurse mentor, family violence liaison worker.

• MAINTAIN PRIVACY & CONFIDENTIALITY

• SAFETY FIRST of nurse, women & children

• BE NON JUDGEMENTAL

• MAINTAIN PROFESSIONAL BOUNDARIES your role is to listen, support & refer

• MINDFULNESS Stages of change. Where is the woman up to?

Further inside are four sections entitled:

• **Inquire and Connect** (this section deals with processes for screening including cross-cultural practice and nurse safety – a nursing concern)

• **Assess and Support** (this section deals with the processes following disclosure and includes a section aiming to alert the nurse to the fact that not all women are ready either to disclose or to accept referrals. The section stresses asking about women’s circumstances, supportive listening and was developed with the knowledge that some nurses had difficulty with accepting women’s decision not to leave when they were unready. It also outlines ‘warm referrals’ and gives advice about clinical decision-making when children are at risk

• **Document** (together with the Women’s Legal Resource Service, MOVE developed a guide to objective documentation which would be useful for court purposes should a nurse be required to give evidence in court)

• **Quality Assurance and Routine Practice** (this section includes routine team monitoring, support for nurses experiencing family violence and mindful practice.

Each section outlines the Aims, Guidelines and Implementation issues, and details practice, including which type of nurse – the universal nurse, the nurse mentor or coordinator/team leader – has responsibility for ensuring implementation.

